#### Process control questionnaire

The process control questionnaire is an abridged version of the Tripod survey [36] and queries about daily work circumstances that may result in substandard acts, or active failures [37]. These circumstances are called basic risk factors. Groeneweg distinguishes 11 of these basic risk factors, six of which are specific for the branch in which the Tripod is developed (i.e. the oil industry) and five are generic. These five generic risk factors regard training, communication, organisation, procedures, and incompatible goals. If these factors are not managed properly, they can start a process that can result in a substandard situation. For instance, when existing guidelines or instructions are not available or of insufficient quality, the chance on non-adherence to these guidelines increases, making procedures a risk factor.

In the present study relevant items in the context of CRM evaluation were selected for each of the generic basic risk factors, thereby reducing the number of items from 75 to 28. For each of the statements participants were asked whether they represented their experiences of the last six months (e.g. 'I could not find the information that I needed to accomplish my task'). The participant could answer 'yes', 'no' or 'do not know'.

#### Patient safety culture

The COMPaZ questionnaire [30] was used to measure the patient safety culture in the ICU. The COMPaZ is the translated Dutch version of the Hospital Survey on Patient Safety Culture (HSOPS) [38]. During translation and validation the COMPaZ was slightly altered from the HSOPS which resulted in 11 dimensions instead of 12 by combining two dimensions of the HSOPS and removing two items. Both questionnaires have successfully been used in previous research [30,38-40].

The COMPaZ consists of 40 items that assess the 11 dimensions. Each item posits a statement that has to be rated on a 5-point scale varying from 'strongly disagree' to 'strongly agree' or 'never' to 'always'. In addition, the COMPaZ comprises a subjective rating of the quality of patient safety in the ICU and incident reporting over the last year.

#### Error culture

The Error Culture Questionnaire (ECQ), developed and validated by Van Dyck [35,41] was used to assess shared attitudes towards, and common responses to error on unit level. According to Van Dyck error culture can be split up into four dimensions, i.e. mastery (trying to overcome errors by learning, analysing and correction), aversion (a rigid and negative attitude towards error occurrence and their deliberate covering up), social (sharing and helping) and awareness (a general readiness to handle errors). Each dimension consists of two or three scales, with a total of 11 scales for all dimensions. These scales are measured with 47 items. Each item is a statement regarding one of the 11 scales. Participants have to rate to which extend this statement applies to the unit on a 5-point scale, varying from 'not at all' to 'completely'. The ECQ has been successfully used in previous research [35,41,42].

#### Job satisfaction and affective commitment to the ICU

Job satisfaction was measured with the Dutch translation [43] of the job satisfaction dimension of the Occupational Stress Inventory (OCI) [44]. The OCI job satisfaction contains six scales that can be used separately. Three scales were selected for the present study (i.e. satisfaction with (1) the job, (2) the organizational design and structure, and (3) the organizational processes). The other three scales were considered to be of less relevance to a CRM evaluation (i.e. appreciation, personal relations, and rewards). The three scales that were used comprised a total of 12 items, which are to be rated on a 5-point scale, varying from 'strongly disagree' to 'strongly agree'. One additional item was added to ask the participant point-blank how satisfied they are with their job (i.e. "Overall, how satisfied are you with your job?").

Affective commitment was assessed with the Dutch translation [45] of the affective subscale of the three component conceptualization of organizational commitment [46]. The questions were slightly altered to the ICU setting by renaming the term 'organization' to 'ICU' in all of the items. The affective commitment scale comprises 6 statements, which are to be answered on a 5-point Likert scale, varying from 'not at all' to 'fully applicable'.

#### Demographics

Several demographic characteristics were administered, including age, gender, position, tenure, experience with working in the hospital and in the ICU, working hours per week, and whether or not the participant has interaction with patients.

### Observation of non-technical skills

Direct observations were used to determine the use of non-technical skills by the IC staff who had direct contact with patients. To assess non-technical skills, an observational model of the Royal Dutch Airlines was used (i.e. SHAPE) [47], which was adjusted for health care (Explicit Professional Oral Communication measurement (EPOC); development and psychometric results will be published separately).

The EPOC classifies explicit professional oral communication of an observed person into six dimensions; assertiveness, working with others, task-oriented leadership, people-oriented leadership, situational awareness, and planning and anticipation. Each dimension is subdivided into several concrete verbal behaviours that together represent the dimension. Throughout an observation of 30 minutes an independent observer tallies how often each verbalization is displayed by the observed person, e.g. 'asks for input', 'coordinates tasks', or 'expresses concerns'. Only professional interaction with co-workers of the ICU was tallied, so social talk or conversations with the patients or family were not tallied.

All observers had a non-medical background in social sciences and were trained for four days. During this training the observers learned the definitions of the verbal behaviours and practised observing at an ICU. To ensure that all observers rated behaviour in the same way and were consistent over time during the data collection period, regular meetings were organized to discuss complex cases. Additionally, 8% of observations were double coded by two independent observers contemporaneously. Furthermore, a 17 minute video of an ICU nurse was used to check the observers' consistency over time. Blinding observers for intervention status of a unit was not possible. Therefore, medical staff was instructed not to discuss the training or CRM issues with the observers and the observers were kept ignorant of the content of the training.

The ICU staff was observed during daily practice, preferably two or three times on different days. All observations took place between 7 am and 7 pm. Each observation had a duration of 30 minutes. At the end of each observation the observed person was asked to fill out the NASA Task Load Index (NASA-TLX) [48] to measure the perceived workload during the observation. The observer independently scored workload as well. Next, the observer filled out which tasks the observed person had done during the thirty minutes of observation, whether there were enough possibilities for professional communication to display non-technical skills, what the level of care the patient received, the number of professional interactions, and with whom.

### Other Measurements

#### Interview implementation progress

Semi-structured interviews were conducted directly after the training and again one year later, to assess if and how CRM had been implemented and what, if any, the stimulating and hindering factors were in this process. Directly after the training the first interview was conducted with one or two persons who introduced CRM to the ICU. The aim of this interview was to discover how CRM came and stayed on the agenda, whether a change team was formed, whether there had been contact with the CRM trainers prior to the training, and whether and how CRM was embedded with existing processes or structures at the unit.

One year after the training, during the second follow-up data collection period, an interview was held with the chairman of the change team. The aim of this interview was to examine whether, and if so, in what ways the ICU had actually implemented CRM after the training. Furthermore, it was asked what their present CRM initiatives were, and what the future directions were. As in the first interview there was special attention to factors that enhanced or hindered successful implementation of CRM. In addition, this second interview aimed to examine the tangible effects of CRM as well as to document the 'do's' and 'don'ts' for future CRM trained departments.

#### Adverse events

Adverse events were assessed using the 'top 9' of adverse outcomes as defined by the adverse outcome committee of the Dutch Association of Intensive Care [49], which are (1) Myocardial infarction; (2) Cardiac arrest, (3) Pneumothorax; (4) Cerebrovascular accident; (5) Critical illness neuro-myopathy; (6) Airway related problems except tracheotomy related problems; (7) Tracheotomy related complications; (8) Problems with vascular access; (9) Bleeding in the proximal and distant digestive tracts. These adverse outcomes were measured using an electronic registration form which was integrated with the digital medical record. Registration was done by the IC physicians as part of the medical record.

#### Patient outcomes

Patient characteristics were registered following current registration standards from the Dutch National Intensive Care Evaluation study [29]. These data were obtained from routine administrative systems following strict definitions and quality checks [50]. Baseline characteristics were collected, using these systems, as defined in the minimal dataset of NICE, which includes general characteristics, such as age, sex, acute and chronic diagnoses, number of admissions, mortality and standardized mortality ratio, Variable Life-Adjusted Display curve, start time and end time of mechanical ventilation, and discharge data from the ICU and hospital. Furthermore, several scoring systems were used to assess the severity of disease(s) and life expectancy of the patient, such as APACHE II [51], APACHE IV [52] and SAPS II [53]. These scores were used to adjust for differences in patient mix. All patient data for this study are anonymous.

#### Additional ICU data - Intake questionnaire

The intake questionnaire assessed basic information about the ICU and was filled out by the head of the ICU. It assessed the number of ICUs within the hospital and the corresponding number of beds per ICU, the total of full time employees, the number of permanent (more than six months) and temporary (less than six months) staff, the percentage of sick leave, participation in NICE registration, the teaching possibilities, the method and use of incident reporting, and the level of the ICU. ICU level refers to the complexity of care that the ICU can manage, varying from a close watch of critical patients for a short number of days (level one) to complex treatment that requires advanced technology and 24 hours per day availability of IC physician (level three). Finally, the intake comprised a question whether the ICU has a closed (specialized IC physician as main clinician) or an open format (the referring physician as main clinician).

### Statistical analyses

The collected data will be checked for completeness and the characteristics and frequency of missing data will be described. Descriptive statistics will be used to describe baseline characteristics of patients, staff and ICU. Comparability of paired intervention and control ICUs will be assessed by comparing baseline data and structural indicators (e.g. number of beds). The effect of the CRM training will be assessed by comparing the before and after measurements of the intervention and control ICUs on all levels of Kirkpatrick's evaluation framework. Changes in patient safety culture, attitude and teamwork behaviour will be described and tested with the ANOVA procedure for repeated measures. This will be done on an individual level with adjustment for the unit. With the observations it is plausible that the different observations within one person will cluster with each other. To control for this clustering, a multilevel analysis will be applied with additional adjustment for the unit. Changes in patient outcomes or incidence of adverse outcomes during the follow-up will be assessed using linear regression analysis while adjusting for case-mix differences and clustering within an ICU.

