## Methods/Design

### Design and setting

Ideally, a CRM training should be evaluated in a large multicenter trial [28]. In our case, time and money were limited, thus we looked for an alternative way to control for institutional variation. We chose for a paired controlled trial, with one pre-test and two post test measurements. Three pairs of comparable ICUs were selected out of a predefined cluster of eligible medium sized units (10 to 16 beds and 55 to 88 employees) of non-academic teaching hospitals. This type of ICU was chosen because these are large enough to form an independent unit, yet small enough to train all of the staff. Moreover, most ICUs in the Netherlands belong to this category or aim to accomplish this. Per pair one ICU received the training directly after the pre-test measurement and one ICU served as a control group. The participating hospitals had on average 641 beds and are located in an urban environment.

Data collection took place from November 2009 until May 2010 (pre-test), June 2010 until September 2010 (post-test 1), and in November 2010 until May 2011 (post-test 2). In each measurement period data were simultaneously collected for the intervention and control unit, and consecutively for all pairs. Per pair each measurement period took 7 to 9 weeks. The intervention units received the training directly after the pre-test. The first post measurement was conducted three months after the training and the second post-measurement followed one year after the training.

ICUs that fitted the profile of a possible intervention unit (i.e. hospital type; ICU size, level and staffing; closed format; taking part in the Dutch National Intensive Care Evaluation (NICE) registry [29]) were approached to participate in the present study (*n *= 12). Most of these ICUs were interested in CRM but unable to fulfil financial needs to start within the study period. Four ICUs were willing to act as an intervention unit and able to pass formal barriers, like finance and organisational arrangements. Of these four, one unit served as a pilot unit, and the other three units served as the intervention group in the main study.

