### Framework of analysis and data collection

The present study uses the evaluation framework for training programmes of Kirkpatrick [32] to determine the effectiveness and cost-effectiveness of CRM training. This framework comprises four levels of evaluation and is often applied in the CRM literature [17,24]. The first level is the reaction of the participant to CRM training. This is followed by the level of learning, which includes the gaining of new knowledge or skills and the constitution of new attitudes. The third level entails whether CRM changes behaviour. The fourth level is the organizational impact, for instance a decrease in the number of adverse events as a result of CRM. Each level is assessed with different measurements at the different data collection periods (see Table 2). In addition to the levels of Kirkpatrick, barriers and facilitators for successful implementation of CRM are assessed, to gain insight in the change process.

**Table 2 T2:** Overview of the measurements for each level of Kirkpatrick

		Measurement properties				Data collection period			
Measurements per Level of Kirkpatrick		# Dimensions	# Items (*k*)	Scale	Fill out time (min)	Baseline	After the training	1st Follow-Up	2nd Follow-up
**I**	**Reaction to the training programme**								
	- End-of-course critique questionnaire*	n/a	21	5-Likert	5		X		
	- Evaluation questionnaire*	n/a	13	5-Likert	5			X	
**II**	**Learning from the training programme**								
	- SafeTeamA questionnaire (attitude towards non-technical skills)	7	43	5-Likert	10	X			X
**III**	**Behavioural change as result of the training**								
	- SafeTeamB questionnaire (perception of the use of non-technical skills)	7	39	5-Likert	10	X			X
	- Process control questionnaire	5	28	Yes/No	5			X	X
	- Observation of non-technical skills	6	30	Count	n/a	X			X
	- Interview implementation progress*	n/a	n/a	n/a	n/a		X	X	X
**IV**	**The impact of the training on the organisation**								
	- - COMPaZ (Patent safety culture questionnaire)	11							
	- Error culture questionnaire	11	47	5-Likert	10	X			X
	- Job satisfaction and affective commitment to the ICU	7	18	5-Likert	5	X			X
	- Intake questionnaire	n/a	n/a	n/a	n/a	X			X
	- Routine administration data	n/a	n/a	n/a	n/a	Continuous			

* These measurements were only collected in the intervention groups

n/a = not applicable

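### Repeated-measures ANOVA drops staff who answered only one of two questionnaire waves a year apart, which costs precision and may bias the between-arm contrast in either direction

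*Protocol article*

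**What the plan says.** Under Statistical analyses the Protocol article names the test for the staff questionnaires: "Changes in patient safety culture, attitude and teamwork behaviour will be described and tested with the ANOVA procedure for repeated measures". It adds: "This will be done on an individual level with adjustment for the unit". The two waves are therefore linked within a person.

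On incomplete data the same section says that "the characteristics and frequency of missing data will be described". It gives no rule for people who answered one wave only.

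Table 2 (Framework of analysis and data collection) marks SafeTeamA, SafeTeamB and the error culture questionnaire at baseline and second follow-up. Design and setting puts the training directly after the pre-test and states that "the second post-measurement followed one year after the training". The entries for the patient safety culture questionnaire (COMPaZ) cannot be read in the text available, so nothing here rests on its waves.

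For the direct observations the plan is different: "To control for this clustering, a multilevel analysis will be applied with additional adjustment for the unit". A multilevel model is thus already part of the plan, but not for the questionnaires.

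**The concern.** Classical repeated-measures ANOVA needs a full set of waves from each person. With two waves a year apart, three groups fall out of the test: staff who left, staff who joined, and staff who were present throughout but returned one questionnaire. The analysed set becomes those who stayed and answered twice.

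Two things are at stake. The first is precision: questionnaires already collected do not enter the test. The second is validity: if the chance of providing both waves depends on the score, and does so differently in trained and control ICUs, the difference in change between arms is distorted.

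There is also a question of scope. The article describes error culture as an attribute of the unit, and its ultimate goal is that CRM becomes embedded in the ICU. A result confined to staff with both waves supports a unit-level statement only in part.

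**Working it through.** The article states no sample size, response rate, turnover or correlation for these scales, so there is no planned figure to reproduce. The calculation below is a scenario.

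**Inputs**
- Staff per ICU: "10 to 16 beds and 55 to 88 employees" (Design and setting); 70 is taken as a round value inside that range.
- Assumed, not in the document: response r = 0.6 or 0.8 at each wave, independent between waves; turnover 12% over the year with leavers replaced; within-person correlation ρ = 0.3, 0.5 or 0.7; SD = 1.

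**Counts per ICU**
- Complete pairs: c = 70 × 0.88 × r².
- One-wave responders at each wave: s = 70r − c.
- r = 0.6: c = 70 × 0.88 × 0.36 = 22.2 (32% of staff), s = 42 − 22.2 = 19.8, s/c = 0.894.
- r = 0.8: c = 70 × 0.88 × 0.64 = 39.4 (56% of staff), s = 56 − 39.4 = 16.6, s/c = 0.420.

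**Variance of the mean change**
- Pairs only: 2(1 − ρ)/c.
- All responders, generalised least squares: 2/[c/(1 − ρ) + s].
- Ratio: 1 + s(1 − ρ)/c.

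An ICU-by-wave variance of 0.02 per wave (assumed) adds 2 × 0.02 = 0.04 to both variances. At r = 0.6 and ρ = 0.3, for example, the ratio is (0.0631 + 0.04)/(0.0388 + 0.04) = 1.31.

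| r | ρ | Variance ratio | Ratio with ICU-by-wave variance |
|---|---|---|---|
| 0.6 | 0.3 | 1.63 | 1.31 |
| 0.6 | 0.5 | 1.45 | 1.20 |
| 0.6 | 0.7 | 1.27 | 1.09 |
| 0.8 | 0.3 | 1.29 | 1.12 |
| 0.8 | 0.5 | 1.21 | 1.07 |
| 0.8 | 0.7 | 1.13 | 1.03 |

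Taking square roots, the standard error is about 6-28% larger with pairs only, or about 2-14% larger once the ICU-by-wave variance is included. With the same rates in both arms, these ratios also hold for the between-arm difference in change.

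**Sensitivity to independent response.** If the same stayers answered both times, c would be 70 × 0.88 × r and s would be 70 × 0.12 × r. Then s/c = 0.12/0.88 = 0.136, and the ratio falls to 1 + 0.136 × (1 − ρ), that is 1.04-1.10 before any ICU-by-wave variance.

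**Bias.** A simulation with no true effect used 400,000 people per arm and ρ = 0.5. About 60% were retained, with retention following a logistic function of the baseline score.

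| Slope of retention on baseline (control, trained) | Contrast, pairs only (SD) | Contrast, likelihood-based (SD) |
|---|---|---|
| 0.5, 0.5 | 0.001 | 0.000 |
| 0.2, 0.8 | −0.109 | −0.002 |
| 0, 0.5 | −0.096 | −0.001 |

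With equal selection, each arm's own change shifts by about −0.09 SD, but the shifts cancel in the contrast. With unequal selection they do not. Swapping the arms reverses the sign.

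**The case against.** **The rule is not written down.** The article names a method and defines no analysis set, and a condensed article may leave the handling of one-wave responders to an analysis plan that is not shown. This is true. But the loss follows from the method that the article does fix, so a later plan would have to replace or supplement the named test.

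**The size is assumed.** This stands. Every rate is an assumption. The loss shrinks when ICU-by-wave variation counts and when the same people tend to respond at both waves.

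**Leaving out joiners is partly right.** The Background criticises earlier studies for not keeping trained and untrained staff apart, and staff who arrive after the course may be untrained. Pooling them changes the question being answered. This stands for attitudes and self-reported behaviour, and less so for unit culture. It gives no reason to discard leavers, or stayers who missed one wave.

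**Stronger readings that the document does not support.** A reader might infer that those who stay and answer twice are the staff most committed to CRM, so that the effect is overstated. No section links commitment to staying or responding; affective commitment is measured only as an outcome. The control ICUs are restricted in the same way. In the simulated cases where high scorers were retained more selectively in the trained arm, the bias ran against the training. A reader might also take the intake item on "the number of permanent (more than six months) and temporary (less than six months) staff" as evidence of expected turnover. It is a descriptive count and yields no rate.

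**Conclusion.** The point holds as a matter of precision and of possible bias. The named test excludes one-wave responders on the SafeTeam and error culture scales. Under the stated assumptions (60-80% response, independent between waves; 12% turnover; ρ of 0.3-0.7) the variance is 1.13-1.63 times larger than it needs to be, or about 1.03-1.31 times with an ICU-by-wave variance of 0.02. With only six ICUs the lower range is the more realistic guide, because variation between units does not shrink when more staff are included.

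Bias in the between-arm contrast is possible, in either direction, if retention or response differs by arm. It reached about 0.1 SD in the scenarios simulated. Equal selection on baseline in both arms leaves the contrast unbiased and mainly limits whom the result describes. The document does not show which situation applies.

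**What to change.** Replace the repeated-measures ANOVA with a likelihood-based linear mixed model that includes everyone who answered either wave. Fixed effects: wave, group and wave × group. Person enters as a random effect, with unit and unit-by-wave terms.

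Alongside it:
- keep the complete-pair analysis as a sensitivity analysis;
- flag staff who joined after the training and show results with and without them;
- report responders, leavers, joiners and the share who attended the training, by unit.

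The change needs no new data, since the named test already requires each person's waves to be linked, and a multilevel model is already planned for the observations. There is a small downside. Including joiners moves the estimand from change within staff towards change in the unit, which is why both versions should be shown. The model relies on data being missing at random, and it does not cure having only six units.

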**Methods/Design:**

Six ICUs participated in a paired controlled trial, with one pre-test and two post test measurements (respectively three months and one year after the training). Three ICUs were trained and compared to matched control ICUs. The 2-day classroom-based training was delivered to multidisciplinary groups. Typical CRM topics on the individual, team and organizational level were discussed, such as situational awareness, leadership and communication. All levels of Kirkpatrick's evaluation framework (reaction, learning, behaviour and organisation) were assessed using questionnaires, direct observations, interviews and routine ICU administration data.

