## Concluding remarks

The present study design is developed to assess the effects of CRM in the ICU, as well as to describe the process that explain such effects. What makes this study unique relative to other CRM evaluations is the combination of the long follow up of one year, the assessment of behavioural change with observations, and the use of matched control units. As recommended and used by several authors [17,23] the framework of Kirkpatrick is employed to distinguish different levels of effect. Besides the observations, a mix of different instruments is used in order to explain the effect on the levels of Kirkpatrick's framework. The matched control units protect the study against secular trends and sudden changes [61].

This study design pays particular attention to practicalities of implementing CRM, by incorporating the assessment of barriers and facilitators to follow up on CRM initiatives developed during the training. This will increase the understanding of the effect of CRM training at the behavioural and organizational level [24]. Furthermore, knowledge on barriers and facilitators will provide a pragmatic start for units that consider training their unit.

Improving the use of non-technical skills of health care professionals in the ICU provides an opportunity to enhance the quality of care and decrease the number of adverse events. CRM appears to take full advantage of this opportunity. It stimulates the individual, as well as the team, to be aware of threats and risks and to manage unsafe situations effectively, for instance by communicating more explicitly. The plans of action resulting from the CRM training provide concrete starting points to implement CRM initiatives, which in turn can create a snowball effect of generic and specific interventions aimed at the improvement of quality and safety of the ICU. These initiatives may improve the management and clinical processes of the unit as well as patient outcomes. By learning from previous research, incorporating new perspectives and keeping an eye on the practical implications, this study design will determine how and to what extent CRM training accomplishes these effects.

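### Staff questionnaire outcomes are tested with individual staff as the error unit although whole ICUs were trained, so ICU-specific change over time is left out of the uncertainty

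*Protocol article*

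**What the plan says.** Under Design and setting, the training is assigned by unit: "Per pair one ICU received the training directly after the pre-test measurement and one ICU served as a control group". The abstract confirms the number of units: "Three ICUs were trained and compared to matched control ICUs". Allocation was not random. The trained units came from those that volunteered and could arrange funding: "Four ICUs were willing to act as an intervention unit and able to pass formal barriers, like finance and organisational arrangements". One of these four served as the pilot, and the other three form the intervention group.

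Under Statistical analyses, the effect of training is the before–after comparison between intervention and control ICUs. Three analyses are named:

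- **Staff questionnaires** (safety culture, attitude, teamwork behaviour): "tested with the ANOVA procedure for repeated measures. This will be done on an individual level with adjustment for the unit".
- **Direct observations**, where repeated observations of one person are expected to cluster: "a multilevel analysis will be applied with additional adjustment for the unit".
- **Patient and adverse outcomes**: linear regression, with adjustment for case mix and for clustering by ICU.

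The Concluding remarks say: "The matched control units protect the study against secular trends and sudden changes".

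**The concern.** The ICU receives the training, but the questionnaire test takes its error from individual staff. In a repeated-measures ANOVA the group-by-time test works on change scores, and a unit main effect, fixed or as a random intercept, cancels out of a change score. It deals with ICUs that are always higher or lower. It does not deal with an ICU whose staff move together between the two measurements because of a new head, a staffing change or another safety project.

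The relevant question is whether three ICU-level changes differ from three others by more than ICUs differ among themselves. Six ICUs give 4 df for that, or 2 df if the pairs are used. An individual-level analysis acts as if there were as many independent replicates as staff.

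A matched control takes out trends that both ICUs of a pair share. It cannot take out a change confined to one ICU, and only the spread between ICUs or pairs shows how large such changes are. What is at stake is the strength of evidence claimed for attitude, self-reported behaviour and safety culture, which are central to the study's aim.

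**Working it through.** **Inputs from the Protocol article.** Six ICUs, three per group; 55 to 88 employees per eligible unit (Design and setting). There is no stated alpha, sample size or intraclass correlation, so there is no plan figure to reproduce.

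**Assumptions.** Two-sided nominal 5% test; m respondents per ICU with both measurements (45 as the working value, 30 to 88 as the range); ρ, the share of change-score variance that lies between ICUs for reasons other than training; equal m, no true effect, and independent ICU changes.

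**Variance.** With the change-score variance set to 1, the difference between the two group means has

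- true variance (2/3) × [ρ + (1 − ρ)/m];
- variance assumed by the individual-level test 2/(3m).

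The ratio is 1 + (m − 1)ρ. If the test instead uses the residual within ICUs (fixed unit-by-time terms, individual error), the ratio is 1 + mρ/(1 − ρ).

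**Type I error.** 2 × [1 − Φ(1.96/√ratio)]. For m = 45:

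| ρ | Ratio, total error | Type I error | Ratio, within-ICU error | Type I error |
|---|---|---|---|---|
| 0 | 1 | 5% | 1 | 5% |
| 0.01 | 1 + 44 × 0.01 = 1.44 | 10.2% | 1.45 | 10.4% |
| 0.02 | 1 + 44 × 0.02 = 1.88 | 15.3% | 1.92 | 15.7% |
| 0.05 | 1 + 44 × 0.05 = 3.20 | 27.3% | 3.37 | 28.6% |

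**Sensitivity to m** (total error):

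| m | ρ = 0.01 | ρ = 0.02 | ρ = 0.05 |
|---|---|---|---|
| 30 | 8.4% | 11.9% | 21.1% |
| 55 | 11.4% | 17.4% | 30.8% |
| 88 | 15.2% | 23.6% | 39.7% |

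**Check by simulation** (10,000 null trials per setting). At m = 40 and ρ = 0.05, the individual-level test rejected in 25.4% of trials, equal to the formula. Adding fixed unit-by-time terms with the individual residual as error gave 26.3%, so that does not help. An unpaired t test on the six ICU mean changes (4 df, critical value 2.78) rejected in 4.6% to 5.5% across settings, and a paired t test on three pair differences (2 df, critical value 4.30) in 4.7% to 5.4%.

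**Price in power.** At m = 40, the difference detectable with 80% power is 2.80 × √(2/120) = 0.36 SD of change if clustering is ignored. With the ICU-level test on 4 df it is 0.57, 0.65 or 0.84 SD at ρ = 0.01, 0.02 or 0.05.

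**Mixed model.** With pair-by-wave fixed, the ICU-by-wave variance rests on 2 df. It is estimated at zero when the between-ICU mean square falls below the within-ICU one, with probability about 1 − exp(−1/ratio), using the within-ICU ratio. At m = 45 this is 1 − exp(−1/1.45) = 50%, 1 − exp(−1/1.92) = 41% and 1 − exp(−1/3.37) = 26% for ρ = 0.01, 0.02 and 0.05. If the term is then dropped, the test reverts to staff-level error.

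**The case against.** The best defence is that the model is not spelled out. The article condenses a fuller plan, adjustment for unit is not defined, and random-effects structure and degrees of freedom are often left to an SAP. That stands as far as it goes. But the article itself commits to an ANOVA on individuals. Only a random unit-by-time effect with small-sample df, or an ICU-level test, would answer the point, and the stated wording does not normally mean either.

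Several stronger readings are tempting, and the documents do not support them:

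- *The test certainly rejects far too often.* With no alpha, respondent number or intraclass correlation stated, the inflation is conditional, and it vanishes at ρ = 0. The differing change teams do not prove background drift: they were formed in trained ICUs as part of the intervention, so they could equally reflect a varying training effect.
- *ICU clustering is ignored for staff.* Unit adjustment is planned for both questionnaires and observations. It is inadequate as worded for the questionnaire ANOVA, not absent.
- *The observation analysis has the same flaw.* It is a multilevel analysis in which the role of unit is undefined. It may or may not include ICU-by-time variation.
- *The matching is discarded.* The article does not say how pairs enter the effect model. Silence in a condensed article is not evidence that they are dropped.
- *An ICU-level analysis would make the comparison sound.* It corrects the interval, not the estimate. A change in one ICU, or the self-selection of the trained units, can still bias the result, and the 5% rate of the ICU-level tests assumes that trained and control ICUs would otherwise change alike.

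**Conclusion.** The point holds for the staff questionnaire outcomes. As written, the group-by-time test uses the wrong error unit for a training delivered to three ICUs and compared with three others, so its p values and intervals are too optimistic whenever ICUs drift separately. The inflation is moderate to large if ρ is between 0.01 and 0.05 (about 10% to 27–29% at m = 45, against a nominal 5%), but both m and ρ are assumed. For the observations, the conclusion is only that the wording leaves open whether the problem is present. This should be corrected before staff-level results are used to claim effectiveness.

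**What to change.** For each staff and observation score, compute the adjusted mean change per ICU and base inference on those ICU-level changes. Preferably show the three intervention-minus-control differences individually, with their mean and a 95% CI on 2 df. An unpaired ICU-level comparison on 4 df is an acceptable alternative.

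If a mixed model is preferred, it is not automatically equivalent. Specify an ICU-by-wave term, and keep that term and its 2 df (4 df unpaired) even when its variance is estimated at zero. For the observations, state explicitly how ICU-by-time variation is handled.

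Do not offer staff-level p values as evidence of effectiveness. State that three self-selected pairs support estimation with wide intervals, and that an event in one ICU can still bias the estimate.

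The cost is analysis wording only, with no new data. The downside is wider intervals and fewer significant results: the multiplier on the standard error becomes 4.30 (2 df) or 2.78 (4 df) instead of about 1.96.
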